# Intravenous lidocaine as an adjuvant to propofol sedation for elderly patients undergoing same-visit bidirectional endoscopy: protocol for a multicenter randomized controlled trial

**DOI:** 10.1080/07853890.2025.2548389

**Published:** 2025-08-20

**Keywords:** Lidocaine, propofol, bidirectional endoscopy, desaturation, hypotension

## Abstract

**Background:**

Same-visit bidirectional endoscopic procedures under sedation are frequently performed in elderly patients. However, the optimal sedation regimen for elderly patients remains uncertain. This study seeks to evaluate the hypothesis that intravenous lidocaine, when used as an adjunct to propofol sedation, reduces the incidence of sedation-related adverse events during these procedures.

**Methods:**

This multicenter, randomized, double-blind, placebo-controlled trial will enroll 648 elderly patients scheduled for same-visit bidirectional endoscopy under sedation at four hospitals in China. Participants will be randomized in a 1:1 ratio to receive either intravenous lidocaine or normal saline (placebo), stratified by study center (*n* = 324 per group). All patients will receive sufentanil (0.1 μg/kg) followed by either lidocaine (1.5 mg/kg) or an equal volume of normal saline, and then propofol (1.0 mg/kg) for induction. Propofol will be titrated to maintain the target sedation level. The primary outcome is a composite of desaturation (peripheral oxygen saturation < 90%) and hypotension (systolic blood pressure < 90 mmHg or > 20% reduction from baseline). Secondary outcomes include total propofol dose, incidence of involuntary body movements, postoperative pain and fatigue scores, and recovery time. Analyses will follow a modified intention-to-treat approach.

**Discussion:**

We hypothesize that adjunctive lidocaine with propofol-based sedation will reduce the incidence of intraoperative desaturation and hypotension in elderly patients undergoing same-visit bidirectional endoscopy. The findings will contribute to optimizing sedation strategies in this vulnerable population.

**Trial registration:**

Chinese Clinical Trial Registry (ChiCTR2400087583)

## Introduction

The incidence of gastrointestinal diseases increases with advancing age, and endoscopic procedures are frequently performed in elderly patients for both diagnosis and therapeutic purposes [1–3]. To improve procedural efficiency and quality of care, an increasing number of elderly individuals opt to undergo esophagogastroduodenoscopy and colonoscopy during the same hospital visit [4]. Sedation is commonly employed during these procedures to enhance patient comfort and procedural satisfaction [5]. However, age-related physiological changes such as reduced drug metabolism and increased sensitivity to sedative agents heighten the risk of sedation-related complications in elderly patients [3]. Accordingly, minimizing sedative exposure is essential for enhancing the safety profile of gastrointestinal endoscopy in this population.

Propofol remains the most widely used agent for intravenous anesthesia in clinical practice due to its rapid onset, short duration of action, and favorable recovery profile [6,7]. Nevertheless, it is associated with dose-dependent adverse effects, most notably hypotension and respiratory depression [8,9]. These complications are particularly concerning in elderly patients and may adversely affect both intraoperative stability and postoperative recovery [9,10]. Intravenous lidocaine has emerged as a promising adjunct to sedation protocols. Prior studies have demonstrated that intravenous lidocaine reduces propofol requirements and alleviates post-colonoscopy visceral pain [11]. Moreover, recent evidence suggests that intravenous lidocaine may significantly improve sedation quality and endoscopist satisfaction, and even reduce the incidence of sedation-related adverse events during endoscopic retrograde cholangiopancreatography (ERCP) procedures [12–14]. It remains uncertain whether the adjunctive use of lidocaine during same-visit bidirectional endoscopy can reduce the incidence of sedation-related adverse events in elderly patients.

This multicenter, randomized, double-blind, placebo-controlled trial is designed to test the hypothesis that lidocaine, administered as an adjunct to propofol sedation, lowers the incidence of desaturation and hypotension during same-visit bidirectional endoscopy in elderly patients.

## Methods

### Ethic approval and trial registration

The study protocol was approved by the ethics committees of the leading center (the First Affiliated Hospital of Soochow University, Suzhou; Approval No. 2024–028) and all participating centers. This trial was registered with the Chinese Clinical Trial Registry (http://www.chictr.org.cn; identifier: ChiCTR2400087583) prior to patient enrollment.

### Study design

This investigator-initiated, multicenter, randomized, double-blind, placebo-controlled trial is being conducted at four hospitals in China. This trial commenced on August 2024, and is expected to conclude on December 2025. Eligible patients must provide written informed consent prior to enrollment. A total of 648 eligible patients undergoing same-visit bidirectional endoscopy will be randomly assigned in a 1:1 ratio to receive either lidocaine or normal saline (324 patients per group). The study flowchart is presented in Figure 1, while Table 1 outlines the schedule for participant enrollment, study interventions, and outcome assessments in accordance with the SPIRIT statement (Supplemental file).

**Figure 1. F0001:**
[figure not shown]
Study flowchart.

**Table 1. t0001:** Schedule of patient enrollment, study interventions, and outcome measurements.

	Study period					
	Enrollment	Allocation	Post-Allocation			Close-Out
	Anesthesia Clinic Visit	Prior to Sedation	During Sedation	Emergence from Sedation	15 Min after Procedure	Hospital Discharge
**Enrollment**						
Eligibility screening	**×**					
Written informed consent	**×**					
Demographic data	**×**					
Baseline characteristics	**×**					
Randomization		**×**				
Allocation		**×**				
**Interventions**						
Lidocaine			**×**			
Normal saline placebo			**×**			
**Measurements**						
Desaturation events			**×**			
Hypotension events			**×**			
Total dose of propofol			**×**			
Involuntary body movement			**×**			
VAS pain scores					**×**	
VAS fatigue scores					**×**	
Recovery time				**×**	**×**	
Injection pain				**×**	**×**	
Dizziness				**×**	**×**	
Headache				**×**	**×**	
Nausea and vomiting				**×**	**×**	
Endoscopist satisfaction			**×**			
Patient satisfaction					**×**	
Sleep score (RCSQ)						**×**
Appetite score (AFSQ)						**×**

According to SPIRIT statement of defining standard protocol items for clinical trials.

Abbreviation: RCSQ: Richards-Campbell Sleep Questionnaire; AFSQ: Appetite and Food Satisfaction Questionnaire

### Eligibility criteria

Eligible participants were (1) aged between 65 and 80 years, (2) American Society of Anesthesiologists (ASA) physical status classification of I to Ш, (3) body mass index (BMI) between 18 and 30 kg/m^2^, (4) scheduled to undergo same-visit bidirectional endoscopy under sedation.

Exclusion criteria were as follows: (1) contraindications to endoscopic procedures or refusal of anesthesia, (2) uncontrolled or potentially life-threatening cardiovascular and respiratory conditions, including acute coronary syndrome, severe uncontrolled hypertension (systolic blood pressure ≥ 180 mmHg or diastolic blood pressure ≥ 110 mmHg), serious arrhythmias, heart failure, acute respiratory infections, asthma exacerbations, active hemoptysis, severe hepatic dysfunction (Child-Pugh class C or higher), acute upper gastrointestinal bleeding with shock, severe anemia (hemoglobin < 6 g/dL), or gastrointestinal obstruction with gastric content retention, (3) absence of an accompanying escort or guardian, (4) known allergies to sedatives or anesthetics, or a significant personal or family history of allergic reactions.

### Randomization and blinding

An independent statistician, who is not involved in the study, will generate the randomization list using an online tool (https://www.sealedenvelope.com/simple-randomiser/v1/lists). Participants will be randomized in a 1:1 ratio using permuted block sizes of 2 and 4, stratified by study center. The randomization assignments will be prepared and sealed in sequentially numbered, opaque envelopes by an independent research assistant who is not engaged in participant recruitment, intervention administration, or outcome assessment. These envelopes will be securely stored until allocation. An independent researcher, responsible for patient enrollment, will open the corresponding envelope to obtain the randomization assignment and prepare the sedation medications accordingly. All patients will receive either lidocaine or normal saline according to the randomization schedule. As both lidocaine and normal saline are clear and colorless solutions, the contents of the syringes will be visually indistinguishable. To minimize the risk of unblinding associated with lidocaine administration, a low dose of sufentanil will be administered at the initiation of anesthesia induction, and intravenous access will be established *via* the antecubital vein [15]. Patients, peri-procedure anesthesiologists, gastroenterologists, and outcome assessors remain blinded to the assigned treatment groups.

### Perioperative management and study interventions

The patient’s vital signs, including heart rate, peripheral oxygen saturation (SpO_2_), and noninvasive blood pressure (measured at 2-minute intervals), are continuously monitored throughout the procedure. All patients will receive oxygen *via* a nasal cannula at a flow rate of 3 L/min for the duration of examination. Gastrointestinal endoscopy is performed sequentially by a team of skilled gastroenterologists at each study center, beginning with gastroscopy followed by colonoscopy. Upon completion of the procedure, patients were transferred to the post-anesthesia care unit (PACU) for postoperative monitoring.

During anesthesia procedures, all agents will be administered at the slowest feasible rate to optimize patient safety and pharmacologic efficacy. Patients in the lidocaine group will receive sufentanil 0.1 µg/kg, lidocaine 1.5 mg/kg, and propofol 1.0 mg/kg administered sequentially at induction. Patients in the saline group will receive an equal volume of normal saline in place of lidocaine, with all other procedures identical to the lidocaine group. Sedation will be titrated by adjusting the propofol dose (typically 0.2–0.3 mg/kg) throughout the procedure to achieve the predetermined target level of sedation. The depth of sedation will be assessed every 30 s using Modified Observer’s Alertness/Sedation scale (MOAA/S) score [16]. At the initiation of gastroscopy, the target sedation depth was set at a MOAA/S score of 1 (only in response to a compressive trapezius stimulus). For the ensuing colonoscopy, the target sedation depth will be adjusted to a MOAA/S of 2 (responding only to light prodding or shaking) [7,17].

Baseline blood pressure will be determined as the average of two measurements obtained while the patient is seated calmly in the preoperative waiting area. Hypotension, defined as a systolic blood pressure (SBP) < 90 mmHg or a reduction of more than 20% from baseline, will be managed with intravenous administration of ephedrine (5–10 mg) or phenylephrine (50–100 μg), as clinically indicated. Bradycardia, defined as a heart rate < 45 beats per minute, will be treated with intravenous atropine (0.3–0.5 mg), or ephedrine bolus if accompanied by hypotension. In the event of hypoxemia (SpO_2_ < 90%), initial management will include a jaw thrust maneuver, increasing oxygen flow to 5–10 L/min, and providing mask-assisted positive pressure ventilation, as necessary. If adequate ventilation cannot be maintained, emergency placement of a laryngeal mask airway or endotracheal intubation will be considered. All adverse events and corresponding interventions will be promptly addressed and thoroughly documented.

### Data collection

Demographic data include age, sex, weight, height, and BMI. Baseline characteristics comprise smoking status, medication history, comorbidities, and ASA physical status. Other peri-procedure variables encompass the total propofol dose, duration of endoscopy, and time to emergence following procedure completion. Hemodynamic parameters, including blood pressure, heart rate, and peripheral SpO_2,_ will be recorded at baseline, after induction, 1 min after procedure initiation, at the end of procedure, and upon emergence. All data will be recorded in electronic case report forms (eCRFs) under the supervision of qualified research personnel. An electronic trial database will be constructed from these eCRFs. Upon completion of data entry, the database will be de-identified and locked. The dataset will then be transferred to an independent statistician for final analysis in accordance with the prespecified statistical analysis plan.

An independent Data Monitoring Committee (DMC) has been established to oversee data integrity and address any issues arising during data collection and registration. The DMC comprises a chair (an experienced anesthesiologist), a pharmacologist, a gastroenterologist and a professor of statistics. In the event of uncertainties or discrepancies related to data collection or registration, the DMC will convene to discuss and reach a consensus resolution.

### Study outcomes

The primary outcome is a composite of desaturation and hypotension events occurring during the procedure [7,17]. Desaturation is defined as peripheral SpO_2_ < 90% for 10 s or longer, while hypotension is defined as a systolic blood pressure (SBP) < 90 mmHg or a reduction in SBP of more than 20% from baseline. The composite endpoint was considered met if either respiratory depression or hypotension occurs in a participant.

The secondary outcomes include (1) total dose of propofol administered, (2) incidence of involuntary body movement during the procedure; (3) postoperative pain score at 15 min after the procedure, assessed using Visual Analog Scale (VAS, 0–10; 0 = no pain, 10 = the most severe pain); (4) fatigue score at 15 min after the procedure, assessed using VAS (0–10; 0 = no fatigue, 10 = extreme fatigue); (5) recovery time, defined as the interval from the end of surgical examination to the point when the patient is able to respond accurately to simple questions (e.g. basic arithmetic). Minimal clinically important differences (MCID) were applied to interpret VAS pain and fatigue scores, defined as a 1-point change on the 0–10 VAS scale for both measures [18,19].

Other outcomes include (1) incidence of other adverse events: injection pain, dizziness, headache, nausea and vomiting; (2) endoscopist satisfaction, assessed on a 5-point scale (0–5; 0 = very dissatisfied, 5 = highly satisfied); (3) patient satisfaction (0–5; 0 = very dissatisfied, 5 = highly satisfied); (4) sleep score on the night following the procedure, assessed using Richards-Campbell Sleep Questionnaire (RCSQ) [20]; (5) appetite score on the first postoperative day, assessed using the Appetite and Food Satisfaction Questionnaire (AFSQ) [21]. Sleep and appetite assessments will be conducted *via* telephone between 7 am and 9 am on the day following the procedure.

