### Statistical analysis

Continuous variables will be assessed for normality using the Shapiro–Wilk test and will be presented as mean ± standard deviation (SD) for normally distributed data, or as median with interquartile range (IQR) for non-normally distributed data. Between-group comparisons will be conducted using the independent-samples t-test or the Mann–Whitney U test, depending on the distribution. Categorical variables will be reported as counts (percentages) and compared using the chi-squared test or Fisher’s exact test, as applicable.

Demographic and baseline characteristics will be summarized using descriptive statistics and standardized mean differences will be reported to assess the balance between groups. For study outcomes, the treatment effects between the two groups will be evaluated using odds ratios (OR) or mean differences (MD), each accompanied by 95% confidence intervals (CI). Additionally, outcomes will be further analyzed using multivariate logistic regression or generalized linear models, adjusting for relevant baseline covariates (age, BMI, history of hypertension, chronic obstructive pulmonary disease [COPD], and diabetes mellitus) and study center. Subgroup analyses of the primary outcome will be conducted to explore potential differential effects of the intervention across predefined subgroups, including BMI (< 25 kg/m^2^ vs ≥ 25 kg/m^2^), history of hypertension (yes vs no), history of COPD (yes vs no), history of diabetes mellitus (yes vs no), and study center (leading center vs participating center), with interaction effects evaluated using logistic regression. Sensitivity analyses will evaluate individual components of the primary outcome and the sedation-related adverse events (desaturation, hypotension, dizziness, headache, nausea and vomiting). Correction for multiple comparisons among secondary outcomes will be performed using the Benjamini–Hochberg method to control the false discovery rate.

All analyses will follow the modified intention-to-treat principle, including all randomized patients who undergo same-visit bidirectional endoscopy under sedation and have available primary outcome data. Protocol deviations are expected to be minimal. No interim analyses or imputation for missing data are planned. All statistical tests will be two-sided, with a P value < 0.05 considered statistically significant. Statistical analyses will be performed using R software (version 4.3.0; R Foundation for Statistical Computing).

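### Propofol is dosed per kilogram, but its secondary outcome is an unscaled total and the adjusted model omits body weight: a small, avoidable loss of precision

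*Protocol article*

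**What the plan says.** Under Perioperative management and study interventions, the lidocaine arm receives "lidocaine 1.5 mg/kg, and propofol 1.0 mg/kg administered sequentially at induction". The saline arm receives saline in place of lidocaine, "with all other procedures identical to the lidocaine group". Sedation is then maintained by "adjusting the propofol dose (typically 0.2–0.3 mg/kg) throughout the procedure". All propofol in both arms is thus expressed per kilogram.

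Under Study outcomes, the first secondary outcome is "total dose of propofol administered". No unit is given and no division by weight is mentioned.

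Under Data collection: "Demographic data include age, sex, weight, height, and BMI". Weight is therefore available for every patient.

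Under Statistical analysis, the comparison named first is unadjusted: "Between-group comparisons will be conducted using the independent-samples t-test or the Mann–Whitney U test, depending on the distribution". A further model adjusts for "age, BMI, history of hypertension, chronic obstructive pulmonary disease", diabetes and study center. Weight, height and sex are not on that list.

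**The concern.** If every dose is weight times a per-kilogram amount, the total is body weight multiplied by the patient's per-kilogram requirement. Treatment can act only on the requirement, and only on its top-up part, since the induction amount is set equal in the two arms. Weight then adds spread that has nothing to do with lidocaine. BMI removes some of it, but BMI divides out height, so the height-driven part of weight stays in the residual.

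Propofol sparing is the main mechanism that the Introduction and Discussion offer for fewer cardiorespiratory events, and the result will be used to interpret the primary comparison. The outcome also shares a Benjamini–Hochberg correction with four other secondary outcomes. A wider interval than necessary is therefore a real, if modest, cost.

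**Working it through.** **The plan's own figure.** No SD, effect size or power is stated for propofol dose. The only sample size is for the primary composite. Pilot rates of 16% and 14% add to 30%, against a target of 20%, with two-sided α 0.05 and power 80%. The unpooled formula gives n = 7.849 × (0.30×0.70 + 0.20×0.80) / 0.10² = 290.4, which matches the stated 290 per group. I use 290 per arm below.

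**Assumptions (not in the documents).** Height has mean 1.63 m and SD 0.06–0.08 m. BMI has mean 23.5 and SD 2.0–3.2, cut to the eligibility range of 18–30. These give a mean weight of about 63 kg with a coefficient of variation (CV) of 0.11–0.15. Top-ups have mean 1.0 mg/kg and SD 0.3–1.0. Adding the fixed 1.0 mg/kg gives a requirement with mean 2.0 mg/kg and CV 0.15–0.50. Weight and per-kilogram requirement are taken as independent.

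**Unadjusted variance ratio.** For a product of independent factors, the squared CV of total mg divided by that of mg/kg is 1 + CV_W² + CV_W²/CV_R².
- Low end: CV_W 0.112, CV_R 0.50: 1 + 0.0125 + 0.0125/0.25 = 1.06.
- Middle: CV_W 0.128, CV_R 0.25: 1 + 0.0164 + 0.0164/0.0625 = 1.28.
- High end: CV_W 0.151, CV_R 0.15: 1 + 0.0228 + 0.0228/0.0225 = 2.04 (simulation: 2.03).

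**After BMI adjustment.** What remains of weight is height squared, with CV about 2×0.06/1.63 = 0.074 to 2×0.08/1.63 = 0.098. The ratio becomes roughly 1 + CV_W² + CV_H²/CV_R², where CV_H is that remaining CV.
- Low end: 1 + 0.0164 + 0.0054/0.25 = 1.04.
- High end: 1 + 0.0228 + 0.0096/0.0225 = 1.45.

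**After weight adjustment.** Only 1 + CV_W² is left, about 1.01–1.02, so weight as a covariate recovers nearly all the loss.

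**Power at 290 per arm, two-sided 0.05 (simulated SDs)**

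| Reduction in total dose | Top-up SD (mg/kg) | Total mg, unadjusted | Total mg, BMI-adjusted | mg/kg |
|---|---|---|---|---|
| 5% | 0.3 | 81–89% | 92–95% | 98% |
| 5% | 0.5 | 53–59% | 60–63% | 67% |
| 5% | 0.7 | 35–37% | 37–39% | 40–41% |
| 5% | 1.0 | 21% | 21–22% | 22–23% |
| 10% | 0.5 | 98–99% | over 99% | 99.8% |
| 10% | 0.7 | 88–90% | 90–92% | 93% |
| 10% | 1.0 | 63–65% | 65–66% | 67% |

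For a 10% reduction with SD 0.3, all are about 100%. For a 25% reduction, power is at least 99.8% at any total-dose CV up to 0.6. The smallest relative reduction detectable with 80% power is CV × √(2/290) × 2.802: 4.2% at CV 0.18, 7.0% at 0.30 and 11.6% at 0.50.

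**What a 5% reduction means here.** With an assumed mean total of 2.0 mg/kg, half of it fixed induction, a 5% fall is 0.1 mg/kg, or a 10% fall in top-ups. A 25% fall in the total needs top-ups halved.

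**The case against.** **Total dose is a legitimate outcome.** The colonoscopy trial cited in the Discussion is reported in mg (58 against 121), so a total keeps comparability. The article prints no unit, and an analysis plan not shown may scale the dose. This stands in part: raw mg is the natural reading but an inferred one, and the total should remain in the report. The article does, however, fix the outcome wording and the covariate list, and neither brings in weight.

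**The effect may be too large for this to matter.** The cited reduction is (121 − 58)/121 = 52%, at which power is near 100% on any scale. But that trial used a lidocaine infusion, and this protocol gives a single bolus without one. With 1.0 mg/kg fixed at induction, anyone above 58 kg receives more than 58 mg before titration starts. The cited effect is therefore no safe guide to the one expected here.

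**The independence assumption is untested.** Top-ups are titrated to sedation depth. If need rises less than proportionally with weight, the advantage of mg/kg shrinks. This stands, and it favours the covariate, which estimates the slope from the data.

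**Stronger readings that the documents do not support.**
- A reader might infer that body size biases the contrast. Allocation is 1:1 randomised, and chance imbalance is already in the standard error. Even with a weight SD of 10 kg, the standard error of the weight difference is 10 × √(2/290) = 0.83 kg, or about 1.7 mg at 2.0 mg/kg against a mean of 126 mg (63 kg × 2.0).
- A reader might infer that the trial is too small. With weight 63 kg (SD 10) and requirement 2.0 mg/kg (SD 0.5), the ratio is 1 + 0.0252 + 0.0252/0.0625 = 1.43, which could be read as needing 43% more patients. That figure rests on assumed SDs, covers only the unadjusted comparison, and concerns an outcome on which the trial was not sized.
- A reader might infer that the post-induction dose gives a stronger test. If induction is exactly 1.0 mg/kg, subtracting it changes neither the absolute difference in mg/kg nor its SD. Only the relative effect looks larger.

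**Conclusion.** The point holds as a minor inefficiency, not an error or contradiction. A measured baseline variable that drives the outcome is left out of its analysis, and BMI is only a partial substitute. Over the assumed ranges, the excess relative variance is about 1.1–2.0 times unadjusted and 1.04–1.45 times with BMI. The loss of power is material only for reductions in total dose near 5% when top-up requirements vary little to moderately (SD 0.3–0.5 mg/kg). It is a few percentage points or less for 10% reductions and negligible for 25% or more. These figures depend on SDs that the article does not give and on weight being independent of the per-kilogram requirement. The direction follows from the dosing rule if dose given rises roughly in proportion to weight. The primary outcome, its test and the sample size are not touched.

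**What to change.** For the propofol outcome, do one of the following before the database is locked and unblinded:
- Add body weight as a covariate in the model for propofol dose, and name that adjusted estimate as the main result for this outcome, because the unadjusted test would otherwise keep the weight variance.
- Or define the outcome as mg per kg actual body weight, which also improves the unadjusted comparison.

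In either case, state the unit and keep total mg as a descriptive line for comparison with published results. Post-induction mg/kg may be reported to show the part of the dose that treatment can change, as an aid to interpretation only.

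The cost is one or two lines of text. Weight and dose are already recorded, and no procedure, sample size or primary analysis changes. If mg/kg becomes the main scale, comparison with results published in mg relies on the descriptive line.
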